### Research aim

The aims of the Future Innovations in Novel Detection of Atrial Fibrillation (FIND-AF) study are to:

Develop a deep learning model for predicting the risk, *and evolution of the risk,* of new-onset AF in primary care.Identify and quantify the magnitude of risk markers of new AF among routinely collected primary care data.Externally validate the model in a geographically distinct dataset to assess generalisability.

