The extracted datasets, including linked data, comprise all patients for the period between 2 January 1998 and 30 November 2018 from the snapshot of CPRD-GOLD and CPRD-AURUM provided in October 2019. Over this study period, the CPRD-GOLD dataset comprises approximately 4.5 million patients eligible for data linkage at an up-to-standard practice, with over 200 000 patients having a record of AF. The CPRD-AURUM dataset comprises approximately 18 million patients eligible for data linkage, with almost 800 000 patients having a record of AF. A sample of 245 general practices will be randomly selected from 800 general practices in CPRD-AURUM to approximately match the size of CPRD-GOLD.

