### Inclusion and exclusion criteria

The study population will comprise all available patients in CPRD-GOLD and CPRD-AURUM eligible for data linkage and with at least 1-year follow-up in the period between 2 January 1998 and 30 November 2018. Patients will be excluded if they were 18 years of age or under at the date of the first registration in CPRD, diagnosed with AF or atrial flutter (AFl) before 1 January 1998, registered for less than 1 year in CPRD or ineligible for data linkage.

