### Outcome ascertainment

The outcome of interest is first diagnosed AF or AFl after baseline (1 January 2009). We have included AFl as an outcome since it has similar clinical relevance, including thromboembolic risk and anticoagulation guidelines, as AF.^1^ These will be identified using Read codes and SNOMED CT in CPRD datasets. For HES APC events and underlying cause of death variable in the ONS Death Registration data file, the 10th revision of the International Statistical Classification of Diseases and Related Health Problems (ICD-10) codes will be used. Misclassified data can lead to systematic prediction errors and accuracy of data may vary over time.^29^ CPRD has converted older ICD codes to the newer version, increasing confidence in their validity. Nonetheless, to verify data accuracy, we will check the data accuracy by year and include the year of AF diagnosis in the prediction models to assess their impact.

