### Predictor variables

A systematic review has highlighted 22 predictor variables included in varying combinations by 10 preceding prediction models developed to detect incident AF in the community.^16^ In addition, a more recently published machine learning model has established six further time-varying variables (eg, change in body mass index between the latest two quarters).^19^

To capture the full potential of deep learning and this large dataset, we will broaden our search for candidate predictors to all available variables, while retaining temporal information (including all clinical assessments, hospitalised events and medications). The potential predictors may include the following:

Sociodemographic variables including age, sex, ethnicity and indices of multiple deprivation.All disease conditions during follow-up, including hospitalised diseases and procedures, such as other cardiovascular diseases, diabetes mellitus, chronic lung disease, renal disease, inflammatory disease, cancer, hypothyroidism and surgical procedures.Clinical assessments including heart rate, systolic and diastolic blood pressure, height, weight and body mass index.Medications prescribed including antihypertensives, statins, antidepressants, anxiolytics/hypnotics and antipsychotics.Lifestyle factors including smoking status and alcohol consumption.All biomarkers routinely collected during follow-up including total, high-density lipoprotein and low-density lipoprotein cholesterol, triglycerides, creatinine, C reactive protein, erythrocyte sedimentation rate.

Predictive factors will be identified using the appropriate codes. In CPRD, we will use Read codes for diagnoses, measurements (eg, systolic and diastolic values) and product codes (prodcodes) for medications. In HES APC, we will use ICD-10 codes and Office of Population Censuses and Surveys Classification of Interventions and Procedures version 4 (OPCS-4) codes. In the ONS Death Registration data file, we will use ICD-10 codes (and ICD-9 codes for the period before 2001).

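### The AF/AFl exclusion stops at 1 January 1998 but baseline is 1 January 2009, so people first diagnosed in between stay eligible for a new-onset cohort

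*Protocol article*

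**What the plan says.** Three places in the protocol article fix the dates.

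- **Data sources and permissions:** the extracts "comprise all patients for the period between 2 January 1998 and 30 November 2018".
- **Inclusion and exclusion criteria:** patients are eligible "with at least 1-year follow-up in the period between 2 January 1998 and 30 November 2018". The only exclusion for prior disease is for those "diagnosed with AF or atrial flutter (AFl) before 1 January 1998". The same criteria apply to GOLD and AURUM.
- **Outcome ascertainment:** "The outcome of interest is first diagnosed AF or AFl after baseline (1 January 2009").

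The Research aim gives the target as the risk, and the evolution of risk, "of new-onset AF in primary care". Predictor variables opens the candidate list to every variable available, with its timing, including medications and "All disease conditions during follow-up, including hospitalised diseases and procedures". It states no exception for AF or AFl codes.

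**The concern.** A model for new-onset disease needs a cohort that is free of the disease at its own time zero. Here the disease-free condition is set one day before the data window opens, and time zero falls 11 years later. A person first diagnosed in, say, 2004 passes every stated eligibility rule, is in the cohort in 2009, and cannot develop AF for the first time afterwards.

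Three things are at stake:

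- **The label.** These people are wrongly classified under either reading of the outcome.
- **The performance estimate.** If prior AF can be seen by the model and repeat codes count as events, the model partly predicts AF from AF. Ethics and dissemination defines success as at least 5% better predictive accuracy than existing models, and the Introduction quotes existing AUCs of 0.725 and 0.827. Inflation from this source could look like success.
- **The risk-marker aim.** Weights given to markers are estimated partly in people who already have the disease.

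External validation would not reveal the problem, because AURUM is selected by the same rule.

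**Working it through.** **1. The gap between the dates** (dates from Data sources, Inclusion and exclusion criteria, and Outcome ascertainment)

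- 2 January 1998 to 1 January 2009: 4017 days; 4017 / 365.25 = 11.0 years.
- 2 January 1998 to 30 November 2018: 7637 days = 20.9 years.
- Share before baseline: 4017 / 7637 = 52.6%.
- Follow-up after baseline: 7637 − 4017 = 3620 days = 9.91 years.

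**2. How a person first diagnosed in the gap is labelled**

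| Reading of the outcome | Label | Why it is wrong |
|---|---|---|
| First ever AF/AFl, dated after baseline | Non-case | Has AF already; not at risk |
| First AF/AFl record found after baseline | Case, if coded again | Old AF counted as new |

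**3. How many people**

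The documents give AF records over the whole window: GOLD "with over 200 000 patients having a record of AF" and AURUM "with almost 800 000 patients having a record of AF". They do not split them at 2009. Assume 30% to 60% of first records fall before baseline:

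- GOLD: 0.30 × 200 000 = 60 000; 0.60 × 200 000 = 120 000. An even spread (52.6%) gives about 105 000.
- AURUM sample, assuming practices of equal size: 800 000 × 245/800 = 245 000 AF records; 30% to 60% is 73 500 to 147 000.

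These are upper limits on the number misclassified. Some of these people died or left before 2009, and the totals may include pre-1998 AF that is already excluded.

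**4. Effect on AUC and positive predictive value**

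Assumed: 1.7% of the cohort prevalent, 1.6% incident, true AUC 0.79 in AF-free people. The remaining share is 1 − 0.017 − 0.016 = 0.967.

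*(a) Prevalent people labelled as cases, AF code visible, all re-coded.* The code separates them perfectly (AUC 1.0), so the apparent AUC is a weighted mean over cases:

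(0.016 × 0.79 + 0.017 × 1.0) / (0.016 + 0.017) = 0.02964 / 0.033 = 0.898.

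With 1% prevalent: 0.02264 / 0.026 = 0.871. With 3%: 0.04264 / 0.046 = 0.927. If only half are re-coded (1.7% prevalent), it is about 0.86.

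*(b) Labelled as non-cases, AF code visible.* The model learns to rank them at the bottom:

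(0.967 × 0.79 + 0.017 × 1.0) / (0.967 + 0.017) = 0.7809 / 0.984 = 0.794.

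*(c) Labelled as non-cases, AF code hidden.* They keep their high-risk profile. In a simulation with these inputs they make up about 10% of the top 5% by predicted risk. Positive predictive value there is 8.9%, against 9.5% to 9.9% in an AF-free cohort (9.9% if they are simply removed, 8.9 / 0.90; 9.5% if the top 5% is chosen afresh).

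Cases (b) and (c) cannot both apply: one needs the AF code seen, the other needs it hidden.

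**5. The stated sample size**

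With 200 parameters, shrinkage 0.95 and Cox-Snell R² 0.01: n = 200 / [(0.95 − 1) × ln(1 − 0.01/0.95)] = 377 996, as stated; 0.017 × 377 996 = 6425 (truncated), as stated. The exclusion date does not enter this formula. After removing 60 000 to 120 000 people, about 80 000 to 140 000 GOLD records would remain as incident AF before other losses, far above 6425.

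**The case against.** The strongest reply is that the intent is plain. The article speaks throughout of new-onset and first diagnosed AF, it condenses a fuller approved application, and the analysts may well drop earlier AF in practice. That stands as a comment on intent: the documents do not show that contamination will occur. It does not repair the text. This is not a detail left to another document. The exclusion is stated, with a date, and the date does not match the stated baseline. The word first defines the outcome, not who is eligible.

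Four stronger readings are tempting and are not supported.

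- **That AF codes will certainly be predictors.** The candidate list is of variables that may be included, and its examples refer to other cardiovascular diseases, which could mean diseases other than AF. The breadth of the list, the inclusion of medications, the lack of any exception, and the plan to put year of AF diagnosis into the models make the inference reasonable, but it remains an inference.
- **That about 105 000 GOLD patients are misclassified.** This needs an even spread of diagnoses over the window and ignores deaths and departures before 2009.
- **That prevalent cases equal the expected new cases.** The Sample size section applies the same 1.7% prevalence to the number who develop AF, so the comparison is circular.
- **That the 1998 date is the error.** A 2009 baseline leaves 9.91 years of follow-up for a longest horizon of 10 years, so the baseline date could be the one that is misplaced. The documents do not settle this.

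**Conclusion.** The eligibility rule and the outcome definition are inconsistent as written. Followed literally, they leave prevalent AF in a cohort meant to predict new-onset AF, in both datasets and under either reading of the outcome. This rests on the dates alone and needs no assumption.

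The size is less certain. The number affected is not given; at most about 60 000 to 120 000 in GOLD follows from the assumed 30% to 60%. The effect on performance depends on the reading. As non-cases, these people shift the AUC from 0.79 to about 0.794, or lower the top-5% positive predictive value by about one percentage point or less. A reader might infer that the reported AUC will be inflated to 0.90. That is a worst case, which needs the looser outcome reading, complete re-coding after baseline and a visible AF code together, at an assumed 1.7% prevalent and 1.6% incident. It is worth preventing because it would be mistaken for success, but the documents do not show that it will happen.

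**What to change.** Reconcile Inclusion and exclusion criteria with Outcome ascertainment:

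- Exclude anyone with an AF or AFl record in CPRD or HES APC on or before baseline, in both GOLD and AURUM. That date is 1 January 2009 if this baseline stands. If any other prediction date is used, apply the same rule at that date.
- State the baseline date once and use it for both eligibility and outcome.
- Restate the eligible numbers and the numbers of incident cases after the exclusion.

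With this rule no AF code recorded up to baseline remains in the cohort, so the question of prior AF codes as inputs falls away. The cost is one line of text, a change to the extraction code, and smaller stated cohort and AF counts. The required 377 996 patients is unaffected.

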### Outcome ascertainment

The outcome of interest is first diagnosed AF or AFl after baseline (1 January 2009). We have included AFl as an outcome since it has similar clinical relevance, including thromboembolic risk and anticoagulation guidelines, as AF.^1^ These will be identified using Read codes and SNOMED CT in CPRD datasets. For HES APC events and underlying cause of death variable in the ONS Death Registration data file, the 10th revision of the International Statistical Classification of Diseases and Related Health Problems (ICD-10) codes will be used. Misclassified data can lead to systematic prediction errors and accuracy of data may vary over time.^29^ CPRD has converted older ICD codes to the newer version, increasing confidence in their validity. Nonetheless, to verify data accuracy, we will check the data accuracy by year and include the year of AF diagnosis in the prediction models to assess their impact.

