### Sample size

To develop a prognostic prediction model, the required sample size may be determined by three criteria suggested by Riley *et al*.^30^ For example, suppose a maximum of 200 parameters will be included in the prediction model and the Cox-Snell generalised R^2^ is assumed to be 0.01. A total of 377 996 patients will be required to meet Riley’s criterion (1) with global shrinkage factor of 0.95; this sample size also ensures a small absolute difference (Δ<0.05) in the apparent and adjusted Nagelkerke R^2^ (Riley’s criterion (2)) and ensures precise estimate of overall risk with a margin of error <0.001 (Riley’s criterion (3)). According to the Quality and Outcomes Framework, the prevalence of AF in England is 1.7%.^31 32^ Given an AF prevalence of 1.7%, only 6425 patients will be expected to develop AF from 377 996 patients. Therefore, the number of patients in the CPRD dataset with AF will provide sufficient statistical power to develop and validate a deep learning prediction algorithm with the predefined precision and accuracy.

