Finally, Transformers have become state of the art in natural language processing,^53 54^ and we will apply an adaption for EHR, BEHRT (BERT [Bidirectional Encoder Representations from Transformers] for EHR), which was originally developed in CPRD.^55^ This model’s structure, depicting each diagnosis code as a word, with each visit as a sentence and the entire medical history as a document, facilitates multihead self-attention, positional encoding and masked language model for EHR. BEHRT can define a representation incorporating information on the diseases afflicting a patient, the positional interactions of diseases and sequence of events, with the age of a patient linked to each visit to give a sense of time between diagnoses.^55^ This representation can then be used for a number of tasks including disease prediction.

Preprocessed patient-level data in CPRD-GOLD will be randomly split into an 80:20 ratio to create training and testing samples. The split ratio is not a significant factor, given the volume of the sample size. The model parameters and dropout rate will be chosen through a grid search and 10-fold cross-validation will be used (ie, 10% of the training data will be randomly selected as the cross-validation set).

While the outcome is binary, instead of just predicting 0 or 1 for a patient (new AF or not), the probability of that patient developing AF by different time points over months (1, 3, 6) and years (1, 5, 10) may be predicted. The probability of developing AF at each time point could be plotted to give an understanding of evolving risk of AF. The clinical risk prediction performance of the deep learning models will be compared against a range of classic machine learning techniques and traditional statistical predictive modelling methods including support vector machine, random forest, naïve Bayes and Cox proportional hazards model. Discrimination (Harrell’s c-statistic and AUC) and calibration metrics will be supplemented with positive and negative predictive values, precision, recall and area under precision-recall curve for all models.

The CPRD-AURUM dataset will then externally validate the model performance to assess generalisability. It has been shown that a lack of external validation has hampered the implementation of previous machine learning models in routine clinical practice.^56^

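### Year of AF diagnosis is to be entered in the prediction models, although it is derived from the outcome and is unknown when a prediction is made

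*Protocol article*

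**What the plan says.** Four parts of the protocol article bear on this point.

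- **Outcome ascertainment** defines the target: "The outcome of interest is first diagnosed AF or AFl after baseline (1 January 2009". It then notes that the accuracy of coded data may change over the years and plans two responses in one sentence. The first is descriptive: "to verify data accuracy, we will check the data accuracy by year". The second is a model term: the team will "include the year of AF diagnosis in the prediction models to assess their impact".
- **Inclusion and exclusion criteria** removes patients "diagnosed with AF or atrial flutter (AFl) before 1 January 1998" and requires patients "with at least 1-year follow-up in the period between 2 January 1998 and 30 November 2018". AF first recorded from 1998 to 2008 is not expressly excluded.
- **Development and external validation of model** says what is to be predicted: "the probability of that patient developing AF by different time points over months (1, 3, 6) and years (1, 5, 10) may be predicted".
- **Missing data** limits chained imputation to baseline covariates with at most 40% missing and adds median imputation as a robustness check.

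Nowhere does the article give diagnosis year a value for patients without AF, replace it with a year known for everyone, or keep it out of the models whose performance will be reported.

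**The concern.** A predictor must be known at the moment of prediction. The year in which AF is diagnosed comes into being only when the outcome occurs, so it carries the label into the inputs. It also carries the approximate timing, which is what the predictions at successive horizons are meant to estimate.

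Three things are at stake for any model that includes it. Its discrimination and calibration would say nothing about real predictive ability. It could not be run on a patient whose future is unknown, although the article foresees use in general practice. It would also fail at its stated purpose: a change in performance after adding the term would reflect leakage of the outcome, not the effect of coding accuracy changing over time.

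**Working it through.** **Step 1. The plan's own figures.** The Sample size section says: "suppose a maximum of 200 parameters will be included in the prediction model and the Cox-Snell generalised R^2^ is assumed to be 0.01". It then gives the result: "A total of 377 996 patients will be required to meet Riley’s criterion (1) with global shrinkage factor of 0.95". Riley's criterion (1) is n = P / [(S − 1) ln(1 − R²/S)]. With P = 200, S = 0.95 and R² = 0.01, n = 200 / [(−0.05) × ln(1 − 0.01/0.95)] = 377 996.5, which agrees. The expected number with AF is 377 996 × 0.017 = 6425.9, against 6425 stated. These figures are correct and do not depend on the point at issue. They serve only to show scale.

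**Step 2. What the variable reveals.** Setting the outcome definition beside the exclusion rule gives three possibilities:

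| Recorded year of AF diagnosis | First diagnosis after baseline? |
|---|---|
| 2009 to 2018 | Yes (case) |
| 1998 to 2008 | No (already diagnosed) |
| Blank | No (never diagnosed in the period) |

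The variable therefore determines the outcome. With a single baseline of 1 January 2009 it largely determines the timing too: 2009 means an event within 1 year, and 2009 to 2013 means an event within 5 years.

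**Step 3. Scale of the blanks.** If 1.7% is taken as the proportion who develop AF, as the Sample size section does, about 6425 of 377 996 patients would carry a year and 377 996 − 6425 = 371 571 (98.3%) would not. This is a rough guide, because 1.7% is a prevalence and not the incidence after 2009. At anything near that level the variable is far beyond the 40% limit for chained imputation.

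**Step 4. Discrimination if the year or its blank is visible to the model.** AUC is the probability that a random case is ranked above a random non-case. From the table, ranking years from 2009 onward above everything else puts every case above every non-case, so AUC = 1.0 by definition.

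**Step 5. Discrimination under median imputation.** Suppose blanks are filled with the median year of the cases. A share q of cases has another year and can be told apart from non-cases. The remaining 1 − q must be separated by the other predictors, with AUC equal to A. Then:

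AUC = q + (1 − q) × A

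If diagnoses are spread evenly over the ten years 2009–2018, q = 0.9. The Introduction's two published AUCs serve as A:

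- A = 0.725: 0.9 + 0.1 × 0.725 = 0.9725
- A = 0.827: 0.9 + 0.1 × 0.827 = 0.9827

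A simulation with 377 996 patients and 1.7% events agrees:

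| Target A | Without diagnosis year | Year or blank visible | Blank median-imputed |
|---|---|---|---|
| 0.725 | 0.723 | 1.000 | 0.973 |
| 0.827 | 0.828 | 1.000 | 0.983 |

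The median-imputed column assumes an even spread of diagnoses, leaves out patients diagnosed in 1998–2008, and supposes a model flexible enough to learn that a non-median year signals a case. A single linear term would exploit this less.

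**The case against.** The strongest defence is that this is loose wording for a data-quality check. The phrase stands under Outcome ascertainment and not under Predictor variables, where diagnosis year is not listed. The Abstract promises only risk factors accessible in primary care, and the intended tool is for patients who do not yet have AF. The authors may have meant calendar year, or a comparison of performance by year of diagnosis.

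That may be the intention, but it does not rescue the text. The check by year is a separate clause, so the model term comes on top of it. The predictor list is open-ended and does not exclude the variable. Even as a sensitivity analysis the term fails, because something that encodes case status cannot show how coding accuracy affects a model.

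The defence does rule out several stronger readings that a reader might infer:

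- *The year is missing in every non-case.* The exclusion covers only AF before 1998, so patients first diagnosed in 1998–2008 could be non-cases who carry a year.
- *AUC is 1.0 whatever is done.* It depends on how blanks are handled.
- *The whole check of accuracy by year fails.* The descriptive part does not use the model term and stands.
- *The share of non-cases is known to be 96% to 98%.* The figures behind that are a prevalence (1.7%) and a count of any AF record over 1998–2018 (200 000 of 4.5 million, so 1 − 0.044 = 95.6% without). Neither is the incidence after 2009.

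**Conclusion.** The point holds as a fault in a stated rule. Taken as written, the article enters an outcome-derived variable in the prediction models. A model with that term would reach AUC 1.0 when the year or its missingness is visible. Under median imputation it would reach about 0.97 to 0.98, on the illustrative assumptions given above. The first figure follows from the definitions; the second is an indication of size only. Neither performance could be reproduced in a patient whose outcome is still unknown.

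A reader might go further and conclude that the study's main comparison, or its success criterion of at least 5% better accuracy than existing models, is invalid. The article does not support that, because nothing ties either one to a model containing this term. The damage is confined to models that include it.

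**What to change.** - Delete year of AF diagnosis as a model term and state that it is not a predictor.
- Keep the descriptive check by year and make it concrete: report AF incidence by calendar year and by code source (primary care records, hospital admissions, death registration).
- Report discrimination and calibration by calendar period, for example 2009–2013 and 2014–2018.
- If index dates vary between patients, use the calendar year of the index date, which is known for every patient. With one common baseline of 1 January 2009 that year is constant and adds nothing, so the stratified reporting carries the assessment.

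The cost is one sentence and a few stratified tables. The required sample size does not change.
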